## Abstract

**Background:**

Mild cognitive impairment is an early stage of Alzheimer’s disease. Increasing evidence has indicated that cognitive training could improve cognitive abilities of MCI patients in multiple cognitive domains, making it a promising therapeutic approach for MCI. However, the effect of long-time training has not been widely explored. It is also necessary to evaluate the extent how it could reduce the convertion rate from MCI to AD.

**Methods/design:**

The SIMPLE study is a multicenter, randomized, single-blind prospective clinical trial assessing the effects of computerized cognitive training on different cognitive domains in MCI patients. It is carried out in 7 centers in China. The study population includes patients aged 50–85, and they are randomly allocated to the training or control group. The primary outcome is to compare the conversion rate of MCI within 36-month follow-up. Structural and functional MRI will be used to interpret the effect of cognitive training. The cognitive training comprises a variety of games related with cognitive domains such as attention, memory, visualspatial ability and executive function. We cautiously set 50% reduction in the rate of conversion as estimated effect. With 80–90% statistical power and 12% as the overall probability of conversion within the study period, 600–800 patients are finally required in the study. The first patent has been recruited in April 2017.

**Discussion:**

Previous studies suggested the benefit of cognitive training for MCI, but neither long-time nor Chinese culture were investigated. The SIMPLE designs and utilizes an improved computerized cognitive training approach and assesses its effects on MCI progress. In addition, neural activities explaining the effects on cognition function changes will be revealed, which could in turn to imply more useful therapeutic approaches.

**Trial registration:**

ClinicalTrials.gov Identifier: NCT03119051.

**Electronic supplementary material:**

The online version of this article (10.1186/s12883-018-1100-x) contains supplementary material, which is available to authorized users.

## Background

Alzheimer’s disease (AD) is one of the most common neurodegenerative diseases. Its symptoms usually emerge gradually after the age of 65 and get worse over time. The disease seriously impaired cognitive functions and daily living abilities, posing heavy care and economic burden on patients’ families and the society. The American Cognitive Function and Aging Study (ACFAS) indicates that the prevalence of AD among people over 65 is 6.5% [1]. In Shanghai, one of the most biggest cities in China, the prevalence of cognition impairment in people over 60 in rural regions and over 55 in urban areas are reported to be 7 and 8.38% respectively [2, 3]. The number of AD patients in China is estimated to reach 23.3 million in 2030 [4].

So far there have been a few effective treatment for AD, though cognitive decline may be slowed down by medications like cholinesterase inhibitors and N-methyl-D-aspartate receptor antagonists. Once dementia happens, no treatment could stop or reverse disease progression by now. The latest studies of AD medications, for example, phase II or III clinical trials using monoclonal antibodies for immunomodulatory therapy [5, 6], all failed in the end. In April of 2011, the National Institute on Aging Alzheimer’s Association (NIA-AA) extended the definition of AD and described three stages of AD [7]. The updated diagnostic guidelines describe preclinical stage before dementia: asymptomatic stage with underlying amyloid deposit and neural injury. In the mildly symptomatic predementia stage, mild cognitive impairment due to AD (MCI) is marked by mild symptoms (no interference with independence) with at least one positive biomarker, including β-amyloid deposits or evidence of neuronal injury. Among the three stages in the NIA-AA guideline, MCI is of greatest significance for clinical interventions. First, approximately 10–12% of MCI patients progressed to AD every year and the 3-year MCI-AD conversion rate reached up to 25–30%. Overall, more than 60% of MCI patients developed AD [8]. So interventions for MCI patients are highly necessary. Secondly, presence of cognitive symptoms makes it possible for identification and diagnosis. Finally, since symptoms are relatively mild, patients could cooperate well with various therapeutic interventions.

Pharmacological and non-pharmacological treatments have been greatly concerned about their effects. Donepezil, rivastigmine, galantamine, and memantine are the drugs presently approved by the Food and Drug Administration (FDA) for treatment of AD. However, both cholinesterase inhibitors (ChEIs) and antiglutamatergic treatments are not indicated for MCI patients. A review and meta-analysis concluded that treatment with ChEIs merely affected MCI progression to dementia or improved cognitive test scores [9]. In one study of data from Alzheimer’s Disease Neuroimaging Initiative, MCI patients who received ChEIs with or without memantine were more impaired, showed greater decline in scores, and progressed to dementia sooner than patients who did not receive ChEIs [10].

In addition, as cognitive symptoms of MCI patients are still mild, drug compliance could be another problem. Moreover, costs and side effects of drugs are important negative factors of early medical treatment.

In recent years, cognitive training has gradually become an important therapeutic approach due to its convenience and effectiveness. It describes a group of brain games exercising mental processing ability such as attention, memory, calculation and so on [11]. An increasing number of studies have proved that cognitive training has beneficial effects on delaying cognitive decline in the elderly. The Advanced Cognitive Training for Independent and Vital Elderly (ACTIVE) study which did a 5-year follow-up of 2802 healthy aging people found that there was a significantly smaller proportion of cognitive decline and higher score of living abilities in the intervention group receiving various cognitive training [12]. Similar effects of cognitive training are also found in MCI patients. Sylvie Belleville et al. [13] found that both MCI patients and healthy elders who received an 8-week intervention focusing on teaching episodic memory strategies had better performance in episodic memory assessment than the control group. An randomized clinical trial of 100 MCI patients found that 6-month cognitive training improved significantly cognitive functions of the intervention group in multiple domains and this improvement was well maintained during a 18-month follow-up [14].

However, there are some limitations in present cognitive training [15]. First, not all cognitive domains are involved in the training. For example, in the ACTIVE study [16], participants received training related with the ability of memory, attention and reasoning, while other cognitive domains like visuospatial and executive functions were not involved. Second, in the traditional pencil-and-paper training, difficulty levels hardly vary from person to person according to their different cognitive abilities. In addition, most clinical trials only performed neuropsychological assessment without objective biomarkers or imaging evaluation. Finally, most clinical trials lack a stable longer-term follow-up of a large number of MCI patients.

Computerized cognitive training has been considered as a convenient, flexible and scalable intervention, which might protect cognition from aging and AD [17]. A meta-analysis suggested its efficacy on global cognition, select cognitive domains, and psychosocial functioning in MCI patients [18]. Our preliminary data analysis suggested that computerized cognitive training improved the MCI participants’ cognitive functions. We once performed a human-computer interaction-based comprehensive training for 66 MCI or dementia patients in Shanghai, and found that the training delayed cognitive decline in visualspatial ability [19]. Thus, based on the previous studies, a 3-year follow-up prospective multi-center trial will be conducted for MCI patients to investigate the role of the computerized-cognitive training in cognitive improvement and its possible mechanisms. Neuropsychological assessment and both structural and functional neuroimaging will be used for evaluation at baseline and follow-up.

## Methods/design

### Study aims

The primary aim of SIMPLE is to evaluate the effect of the computerized cognitive training on the conversion rate of MCI to AD in the 3-year follow-up.

The secondary aims of this study are to investigate how the cognitive training affects global cognitive function, daily living function and brain activities, and to determine whether patients should receive such intervention at MCI stage.

The main research topics are:Are there significantly less MCI patients convert to AD if they receive computerized cognitive training in the 3 years period?Could the scores of cognitive assessments and daily living activities be improved after training?Does computerized cognitive training have effect on the brain structure or activities (both regional and neural connectivity) changes? If so, how are they linked with cognitive function?

### Study design

SIMPLE is a 3-year multicenter prospective single-blind clinical cohort study with two parallel arms in 1:1 ratio. Patients are randomized into the training group the control group (absence of training). The total training dose will be around 200 h, with 3–4 sessions per week and 30 min per session. Though dose effect was not well studied, we will give the training dose that is acceptable by MCI patients according to previous studies and our preliminary data. Global cognitive function and daily living activity will be assessed at baseline and every 6 months afterwards (in month 6, 12, 18, 24, 30 and 36), while specific cognitive domains (memory, executive function, attention and language) will be evaluated at baseline and every 12 months afterwards (in month 12, 24 and 36). In addition, brain structure and function will be assessed by MRI at baseline and in month 12 and 36. During the follow-up period, medications for dementia (ChEIs or memantine) are not indicated. If a patients converts to AD during follow-up, pharmacological therapy starts. Cognitive assessments for all cognitive domains and MRI will be performed at that time. Meanwhile, telephone follow-ups will be conducted every two weeks in both groups. As an single-blind trial, neuropsychological assessor will be blinded to the group allocation. The total duration of the study will be approximately 5 years, from June 2017 (first in) until June 2022 (last out).

### Patients

In total, 600–800 MCI patients will be enrolled from memory clinic of four centers in Shanghai, one in Zhejiang Province, one center in Hu’nan Province and one in An’hui Province: Ruijin Hospital affiliated to Shanghai Jiaotong University School of Medicine, Renji Hospital affiliated to Shanghai Jiaotong University School of Medicine, Shanghai General Hospital affiliated to Shanghai Jiaotong University School of Medicine, Shanghai Mental Health Center, Suzhou municipal hospital in Anhui Province, Zhoushan Hospital in Zhejiang Province and Xiangya Hospital in Hu’nan Province. Among them, Ruijin Hospital is the leader of SIMPLE, in charge of patients enrollment, quality control and ethical problems. The inclusion and exclusion criteria are shown as follows.

### Inclusion criteria are

▪ Male or female, aged 50–85;▪ MCI diagnosed according to the National Institute on Aging-Alzheimer’s Association (NIA-AA) workgroups [20];▪ 24 ≤ Mini-Mental State Examination (MMSE) ≤28;▪ The Hamilton Depression Scale/17-item (HAMD) score ≤ 10;▪ Not on medication for dementia (Table 1);▪ MRI T2 weighted imaging (T2WI) scan: if aged ≤70, Fazeca scale for White Matter lesions rating level ≤ 1; if > 70 years, white matter damage rating scale ≤2. The number of lacunar infarcts larger than 2 cm in diameter ≤ 2. No infarcts in hypothalamus, entorhinal cortex, para-hypothalamus, cortical and subcortical cavity infarction near gray matter nuclei. The medial temporal lobe atrophy (MTA) score: Grade II or above.▪ Accompanied by reliable caregivers (at least intensive contact of 4 days every week and 2 h every day) who are expected to participate in the follow-up visits and provide useful information for scores of scales;▪ Education level: primary school (grade 6) or above.▪ Expected good compliance with the therapy and follow-up. Each patient gives a written informed consent, and the study has been approved by Ruijin Hospital’s ethical committees.

**Table 1 Tab1:** Forbidden and restricted medication in the trial

Forbidden medication	Cholinesterase inhibitors
	N-methyl-D-aspartate (NMDA) antagonists
	Synthetic adrenal corticosteroids
	Central nervous system stimulants
	Chinese and western cognitive improvement medication
Restricted medication^a^	Antipsychotics
	Antidepressants
	Sedative-hypnotics^b^

Restricted medication^a^: The dose of these medications should not be increased during the trial. Patients with these medications for a long time should keep the dose stable

Sedative-hypnotics^b^: If necessary, temporary use of zopiclone, alprazolam or estazolam is allowed. Last dose before psychological assessment should not be given later than 22:00 last night

### Exclusion criteria are

▪ Cognitive decline caused by other diseases (including but not limited to: cerebrovascular disease, central nervous system infections, Parkinson’s disease, metabolic encephalopathy, deficiency of folic acid/vitamin B12 and hypothyroidism);▪ Medical history of other neurological disorders (including stroke, Parkinson’s disease, epilepsy, etc.);▪ Psychiatric disorders defined by Diagnostic and Statistical Manual of Mental Disorders (DSM)-IV criteria;▪ Severe disease of heart, lung, liver, kidney or hematopoietic system;▪ History of alcohol or drug abuse;▪ Participation in other clinical trials within 30 days before the screening of this study;▪ Other reasons that make one inability to complete the study.

### Withdrawal criteria are

Patients should withdraw from the trial if they meet the following criteria:▪ Poor compliance to the protocol;▪ A serious complication or other severe disease happens in the trial.▪ Patients refuse to be followed up or become lost at the point of follow-up.

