### Outcome measures

The primary outcome is the incidence of AD during the follow-up. The diagnosis of AD will be made according to NIA-AA criteria. The performance in each cognitive domain will be compared as secondary outcomes. ADAS-Cog will be used to assess the global cognitive performance of MCI patients. Memory will be assessed using the AVLT-H. Attention and executive functions will be evaluated by TMT and the Stroop task. Language will be assessed by Boston naming test (30-item version). Visual spatial ability and visual memory will be evaluated by the Rey–Osterrieth complex figure test (CFT). Activities of daily living will be assessed by ADCS-ADL. Structural and functional MRI will help to uncover the potential neural activity changes during training. The schedule of all the outcome measures is shown in the Table 2.

**Table 2 Tab2:** Outline and timelines of the trial

	Screening	Run-in	Baseline	1st Visits	2nd Visit	3rd Visit	4th Visit	5th Visit	Endpoint^a^
Time Points	−3 weeks	−2 weeks	0	6 months	2 months	18 months	24 months	30 months	36 months
Written informed consent		×							
Inclusion/exclusion criteria	×	×	×						
Blood test		×							
Electrocardiogram		×							
Cranial MRI examination		×			×				×
MMSE	×		×	×	×	×	×	×	×
ADAS-Cog			×	×	×	×	×	×	×
ADCS-ADL			×	×	×	×	×	×	×
HAMD/GDS	×		×		×		×		×
AVLT			×		×		×		×
TMT			×		×		×		×
CFT			×		×		×		×
Stroop Test			×		×		×		×
Boston Naming Test			×		×		×		×

^a^Endpoint is either the ending of 36-month follow-up or the diagnosis of AD during follow-up

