### Sample size and statistical analysis

Sample size was estimated based on conversion rate from MCI to AD in the SAS study [28]. In the SAS sample, it was 6.0 per 100 person-years. In the three-year follow-up, the overall probability of conversion event would be 17%. We use hazard ratio (HR) to represent the converting difference of the training group per unit time as the control group. HR represents instantaneous risk over the all period, and is clinically significant due to its indication risks that happen before the endpoint. A power calculation was performed with the online freeware program by “time-to-event” method [29] (http://powerandsamplesize.com).

Due to HR as an almost unprecedented outcome in such sort of trial, we cautiously set 50% reduction in the rate of conversion as estimated effect. With 80–90% statistical power and 12% as the overall probability of conversion within the study period, 544–728 patients in total are considered the minimal number necessary to estimate the hazard ratio. Considering 10% dropout, we plan to enroll approximately 600–800 patients, with 300–400 patients in each group.

As an exploring study, we used per-protocol set instead of intention-to-treat (ITT) analysis as primary endpoint analysis in order to strictly estimate the effect of training. If participants were indicated cholinesterase inhibitors or memantine, or they could not insist on training, they would be excluded from per-protocol sets. ITT approach will also be done to avoid the effects of crossover and dropout. The results of these two analysis will be carefully interpreted.

The randomization is stratified by age and education years according to the Ruijin center using SAS statistical software (SAS Institute Inc., Cary, NC, USA) by a statistician ([name]) with no access to information on the patients or physicians. Patients will be randomized in a ratio of 1:1 to receive the training or only follow-up. In the randomization process, the randomized code is generated and assigned to physicians in a sealed envelope by the statistician. Afterwards, the sealed randomization codes are sent out to each center. The odd number means the training group, while the even number means the control group. If the patient cannot be trained because of difficulty in operating computer or cellphone, the patient will be managed as off-trial.

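### Withdrawing poor compliers from the trial, with no stated AD ascertainment afterwards, conflicts with the promised ITT analysis and compromises it

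*Protocol article*

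**What the plan says.** The section on withdrawal criteria opens with "Patients should withdraw from the trial if they meet the following criteria". Its first item is "Poor compliance to the protocol"; a separate item covers the case that "Patients refuse to be followed up or become lost at the point of follow-up". The next section, on endpoint criteria, says when patients finish their training: after three years or at a diagnosis of AD dementia.

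Under Outcome measures, "The primary outcome is the incidence of AD during the follow-up". Intervention and follow-up schedules assessments every six months to month 36.

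Under Sample size and statistical analysis, "we used per-protocol set instead of intention-to-treat (ITT) analysis as primary endpoint analysis". Patients for whom cholinesterase inhibitors or memantine are indicated, "or they could not insist on training, they would be excluded from per-protocol sets". The article then adds that "ITT approach will also be done to avoid the effects of crossover and dropout". The same section says that if a patient cannot be trained because of difficulty with the device, "the patient will be managed as off-trial".

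**The concern.** An ITT analysis counters dropout only if outcomes are sought for patients who stop the intervention. Here the withdrawal rule takes poor compliers out of the trial, and incident AD is seen only through continued assessment. The rule therefore creates the missing outcomes that the ITT analysis is supposed to deal with.

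The loss is likely to be uneven. Trainees face 3–4 sessions a week, monitored online, for up to three years, and the device-difficulty rule concerns training only. It is also likely to be informative, because declining cognition is a plausible reason for giving up computer games. Since the per-protocol set is primary, ITT is the only check on that selection the article names, and outcomes that were not collected cannot be recovered at the analysis stage.

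**Working it through.** **1. The passages side by side.**
- The article has wording for ending training (endpoint criteria) and does not use it in the withdrawal section, which speaks of leaving the trial.
- Refusal or loss of follow-up is its own withdrawal item, so the compliance item also reaches patients still willing to be followed.
- No section keeps withdrawn patients in the six-monthly visits or says that their AD status is sought later.
- The statistical section handles the same kind of patient through the analysis set and offers ITT as the counterpart, which presupposes that they are still observed.

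**2. The plan's own figure.** Schoenfeld's formula with 1:1 allocation, HR 0.5 and two-sided alpha 0.05 (assumed; not stated) gives events = 4(1.960 + z)² / (ln 0.5)². That is 65.35 at 80% power and 87.48 at 90%. Dividing by 0.12 gives 544.5 and 729.0, against the stated 544–728. The sample size reproduces and this point does not affect it.

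**3. Illustration of the bias.** Inputs from the article: 600 enrolled, 300 per arm, 270 after 10% dropout; 6.0 conversions per 100 person-years, so a three-year cumulative hazard of 0.18 and a risk of 1 − e^(−0.18) = 16.5% (the article gives 17%). Assumptions not in the article: no true effect; a fraction x of trainees withdrawn at time zero, on top of the 10% dropout; their hazard r times that of the rest; no such loss among controls.

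Control events: 270 × 0.1647 = 44.5. Apparent HR = 1 / ((1 − x) + x·r).

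| x, r | Apparent HR | Training events lost | Training events seen |
|---|---|---|---|
| 10%, 1.5 | 1/1.05 = 0.952 | 27 × (1 − e^(−0.257)) = 6.1 | 243 × (1 − e^(−0.171)) = 38.3 |
| 20%, 2 | 1/1.20 = 0.833 | 54 × (1 − e^(−0.30)) = 14.0 | 216 × (1 − e^(−0.15)) = 30.1 |

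The one-sided false-benefit rate is Φ(−ln HR / SE − 1.96), with SE = √(1/44.5 + 1/training events seen).
- 10%, 1.5: 0.0488/0.220 = 0.22, so Φ(−1.74) = 4.1%.
- 20%, 2: 0.182/0.236 = 0.77, so Φ(−1.19) = about 12%.

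With 800 enrolled (360 per arm) the range is about 4–14%.

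**4. Sensitivity.**
- *Event rate.* With the 12% used for the sample size, at 270 per arm: 3.8–9.7%.
- *Timing.* With hazards set so that the whole arm has 16.5% risk, and censoring at withdrawal, a log-rank calculation for 20% at twice the hazard gives 11.0% at month 0, about 6% at month 12 and about 5% at month 18. For 10% at 1.5 times: 4.0%, 3.4% and 3.1%. At month 18 the apparent HR is about 0.93–0.98.
- *Equal risk (r = 1).* HR 1.0 and 2.5%: no bias.

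**5. Power.** Under the planned HR of 0.5 and 12% overall (15.8% control, 8.2% training), with all 600 counted, losing 10–20% of trainees from the start costs 300 × 0.10 × 0.082 = 2.5 to 300 × 0.20 × 0.082 = 4.9 conversions. Power falls from 83.7% to 82.3–80.5%. The issue is bias rather than power.

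**The case against.** A reader might infer that poor compliers must leave, that their conversions are never seen and that an ITT analysis is impossible. The documents do not support that. The rule says should; conversions before withdrawal are recorded; nothing forbids later ascertainment; and all randomised patients can still be analysed by assigned arm with censoring. This is also a condensed article, and the full protocol may provide for follow-up after withdrawal. All of this stands. What remains is that two stated rules conflict, and the wording given points towards loss of follow-up.

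Nor do controls have nothing to comply with: they are asked to keep their usual habits and take up no cognitive training, and the medication limits in Table 1 are set for the trial, not for one arm. A heavier loss among trainees is therefore probable, not certain. The run-in also assesses compliance and computer operation, though two weeks cannot screen out non-adherence that develops over three years.

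A censored ITT analysis is not identical to the per-protocol analysis either. It keeps time and events before withdrawal, and it keeps patients excluded from the per-protocol set for a medication indication. The overlap in selection is large but not complete.

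Finally, the primary analysis excludes non-trainers whatever the withdrawal rule says, so the rule adds little bias there. This stands and limits the seriousness of the point.

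**Conclusion.** The conflict is real and should be fixed. As written, poor compliers leave the trial, no later AD ascertainment is provided for, and the ITT analysis would rest on censoring that is probably uneven between arms and probably informative. It can be run, but it would not deliver the freedom from dropout effects that the article promises. The added harm falls mainly on that analysis.

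The size is not known from the article. The apparent HR of 0.95–0.83 and the false-benefit rate of about 4–12% rest on assumed shares and hazards and on departure at time zero, so they are upper-end values for those assumptions; withdrawal at month 18 brings the rate to about 3–5%. Whether per-protocol should be primary is a separate question.

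**What to change.** Reconcile the withdrawal criteria with the statistical section by separating stopping training from stopping follow-up. State that a patient who stops training or complies poorly stays in the six-monthly assessments and AD ascertainment to month 36 unless the patient refuses follow-up. Record the date and reason of non-compliance, and analyse these patients in their randomised arm in the ITT analysis. Say also whether patients managed as off-trial for device difficulty after randomisation are followed in the same way.

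This concerns data collection only and changes no treatment rule. The cost is protocol wording plus the effort of retaining non-compliant patients; the visits are already in the schedule, although the article gives no budget from which to judge their expense.
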